#### Usual care

Participants in both trial arms will be able to continue with any existing treatment consistent with the eligibility criteria and will also be permitted to begin any new treatments during the study. Treatment received by YP and parents will be recorded at 9 months using the Client Service Receipt Inventory.^39^

### Adherence

Adherence to the intervention for YP will be defined as attending 6 out of 8 acute sessions and 2 out of 3 continuation sessions. Adherence will be rewarded by providing certificates following completion of the programme. Therapists will also offer sessions scheduled outside the school day and one-to-one catch-up sessions if YP are unable to attend a session. Attendance for each participant will be monitored. For PTO, the opportunity to be assessed and treated by a specialist (psychiatrist) may be attractive, and we will offer flexibility in how parents complete appointments (in person/videocall/phonecall). Adherence to PTO will be defined as completion of the baseline assessment and four follow-up calls.

### Retention

Participants (parents and YP) will each receive £60 in gift vouchers for participation (£10 at baseline, £20 at 3 months, £30 at 9 months) and study completion certificates at 3 months and 9 months. Those who also participate in qualitative interviews and/or focus groups will receive an additional £20 voucher.

### Patient and public involvement

Adaptations to the intervention were made following discussions with the TMG, the CwS intervention developers, professionals and our study advisory group of 12 YP with lived experience of depression/anxiety (YPWLE). The latter advisory group contributed feedback on protocol development during three meetings (two online, one hybrid) and a smaller group contributed on one additional occasion. YPWLE advised on: the study name, assessments, timings of intervention/assessments and adaptation of the intervention (workbook content including language, visuals, online delivery methods). One young person and a parent with experience of depression are members of the independent TSC.

### Outcomes and assessments

Parents and YP will complete assessments with a researcher via videocall at initial screening, at baseline and 9-month follow-up post randomisation. Self-report questionnaires will be completed at baseline, 3 months and 9 months (figure 1). We selected 9-month post randomisation to assess the primary outcome for consistency with prior studies^16^ and because this aligns with completion of the full intervention. The 3-month postrandomisation follow-up was selected to allow for measurement of potential mediators and secondary outcomes following completion of the acute intervention sessions. Table 2 shows the schedule of measures.

**Figure 1 F1:**
[figure not shown]
Participant timeline. SWELL, Skills for Aadolescent WELLbeing; YP, young people.

**Table 2 T2:** Schedule of assessments

	Follow-up			
	Screen	Baseline	Month 3	Month 9
Questionnaires about young people				
Eligibility questions (eg, psychiatric history and treatment)	P			
Centre for Epidemiological Studies Depression Scale	Y	Y	Y	Y
Demographic characteristics (eg, age, sex, ethnicity, education)		Y, P		
Revised Children’s Anxiety and Depression Scale		Y, P	Y, P	Y, P
Affective Reactivity Index		Y, P	Y, P	Y, P
Social Communication Disorders Checklist		P		
DuPaul ADHD Questionnaire		P		
Dysfunctional Attitudes Scale for Children		Y	Y	Y
Generalised Self-Efficacy Scale		Y	Y	Y
Perceived Stress Scale		Y	Y	Y
Behavioural Activation Scale for Depression- short form		Y	Y	Y
Developmental Competence Scale (abbreviated)		Y		Y
Conflict Behaviour Questionnaire		P	P	P
Child Report of Parents Behaviour Scale		Y	Y	Y
Parental monitoring (child disclosure questions)		P	P	P
Life Events Checklist		Y, P		Y, P
EQ-5D-Y		Y		Y
Young person’s experience of the intervention			Y, P	
Interviews about young people				
Development and Well Being Assessment		Y, P		
Client Service Receipt Inventory		Y, P		Y, P
Longitudinal Interval Follow-Up Evaluation				Y, P
Questionnaires about Parents				
Eligibility questions (eg, psychiatric history and treatment)	P			
Patient Health Questionnaire-9	P	P	P	P
Demographic characteristics (including age, sex, ethnicity, education level, income, occupation)		P		
Screen for Adult Anxiety Related Disorders		P	P	P
WHO Disability Assessment Schedule		P		P
Parent’s experience of the parent treatment optimisation		P		
Interviews about parents				
Schedules for clinical assessment in neuropsychiatry		P		
Psychiatric history, using life history calendar approach		P		
Client Service Receipt Inventory		P		P
Longitudinal Interval Follow-Up Evaluation				P
Other Measures				
Depression risk score		Int		Int
Children’s Global Assessment Scale		Int		Int
Global Assessment of Functioning		Int		Int
Hamilton Depression Rating Scale		Int		Int
Parent treatment optimisation adherence checklist		Res		
Young person intervention adherence checklist				Res
Young person intervention fidelity checklist			Res	

In addition to completing these measures, young people and their parents will be asked for consent to data linkage with routine healthcare data (in Wales this is via the Secure Anonymous Information Linkage databank). This will enable further follow-up of study participants to examine longer-term outcomes including depression diagnosis and treatment.

ADHD, Attention Deficit Hyperactivity Disorder; EQ-5D-Y, EuroQol Quality of Life 5 Dimensions; Int, completed by interviewer; P, parent completed; Res, member of the research team; Y, young person completed.

#### Primary outcome

##### Depressive episodes

The primary outcome is the time to a probable Diagnostic and Statistical Manual of Mental Disorders-Fifth Edition^40^ MDD episode in the young person during the 9-month follow-up period. We will collect data about when any depressive episode occurs during the follow-up period using the LIFE,^41^,^43^ a semistructured interview, that uses a life-calendar approach allowing diagnoses and the week-of-onset to be derived. For each week of follow-up, symptoms are rated using the six-point Depression Symptom Rating (DSR) scale, which has good reliability and validity.^43^ A DSR score of >4 for at least 2 weeks will define a depressive episode.^16^ YP and parents will be interviewed with the LIFE about the YP’s depression, with parent and YP reports combined at the diagnosis level consistent with clinical practice.

### Secondary outcomes

These assess the potential effect of the intervention on depression severity and recovery, dimensional measures of mental health problems (depressive symptoms, anxiety symptoms, irritability), depression risk score,^44^ quality of life, functioning and competence. These will be measured using standardised and validated questionnaires/interviews (box 3).

Box 3Description of secondary outcome measuresDepression-free periods during the 9-month follow-upNumber of depression-free weeks, the duration of depression-free periods, time to recovery from depressive episodes and time to recurrence of depressive episodes in the 9-month follow-up period will be measured using the Longitudinal Interval Follow-Up Evaluation (LIFE). 41,43 This semistructured interview (also used to assess the primary outcome) assesses the longitudinal course of depression in enough detail to date individual episodes, allowing calculation of time to recovery, length of depression-free intervals and time to relapse or recurrence. Young people and parents will complete the LIFE about the young person’s depression.Depression symptomsWill be measured using the Centre for Epidemiological Studies-depression scale (CES-D)^51^ completed by the young person. This measure includes 20 items about symptoms in the past week and has good internal consistency across clinical (α=0.83–0.84) and non-clinical samples (α=0.81–0.93).^52^Depression Risk ScoreA Depression Risk Score tool^44^ will be used to assess if the intervention affects the young person’s 3-year risk of developing depression. This score has been developed and externally validated in young people with a parent with a history of recurrent depression.^44^ The risk score is based on age, sex, family income, young person’s symptoms of anxiety, depression and presence of stressful life events in the past 9 months, plus current parent depression symptoms.Anxiety symptomsThe Revised Children’s Anxiety and Depression Scale (RCADS)^52 53^ will be used to measure anxiety symptoms and will be completed by both the young person and their parent.Irritability symptomsIrritability will be measured using the Affective Reactivity Index (ARI).^54^ The ARI is a dimensional measure of irritability containing seven items scored on a 3-point scale and will be completed by young people and their parents.Quality of lifeWill be assessed using the young person report of the EuroQol Quality of Life 5 Dimensions (EQ-5D-Y) which consists of questions about mobility, looking after self, doing usual activities, pain/discomfort, and feeling worried, sad, or unhappy,^55^ plus a vertical visual analogue scale ranging from ‘the best health you can imagine’ to ‘the worst health you can imagine’.Developmental competenceA modified version of the scale used by Brent *et al*^17^ will be completed by the young person. The scale assesses developmental competence (including academic and interpersonal competence) and includes 9 items scored 0–4.Functional impairmentThe Children’s Global Assessment Scale (cGAS)^56^ will be completed by the research interviewer about the young person’s functioning. The cGAS measures psychological and social functioning rated on a scale of 0–100, with a lower score indicating greater impairment.CES-D was selected as the measure of depressive symptoms for consistency with.^16^ The RCADS was additionally included to assess anxiety, and because it is recommended as a common measure of anxiety and depression (https://iamhrf.org/projects/driving-adoption-common-measures).

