### Sample size

We aim to recruit 400 YP and parents/carers, based on a previous study^17^ and sample size calculations. We allow for 10% loss to follow-up based on previous studies of this population and depressed YP.^1630^,^32^ The effect size observed in the study by Garber *et al*^16^ was a HR of 0.63. We expect the effect of the intervention in this RCT to be slightly greater than this due to the addition of PTO before randomisation. We therefore define the minimum clinically important difference for this study as an HR of at least 0.60 (equivalent to an 11% difference in MDD between study arms). With a sample size of up to 400 randomised participants, we estimate statistical power as 79.9% to detect a difference of at least HR=0.60 between study arms, with an assumed 10% attrition rate at 9 months, expected event rate probabilities at follow-up of 0.327 (control) and 0.211 (intervention) based on^17^ a one-sided alpha of 0.05. A HR of 0.56 (equivalent to a 12% difference between study arms) will attain 87.0% power. A STATA V.17 programme was used for this estimation.^33^

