Repeated measures analysis will be used for secondary outcomes collected at 3 months and 9 months. Linear mixed effects regression will be used to account for clustering by group delivery in the intervention arm (partial effect model) and will include baseline values as covariates where appropriate. Where the assumptions of the linear regression model are not met, transformation or categorisation will be considered. Logistic regression models will be used for binary outcomes. Main group effects and 95% CIs will be presented for all outcomes.

Qualitative data analysis will use a thematic analysis approach, a process of identifying, analysing, reporting and interpreting patterns or themes.^48^ Codes will be applied to broad themes and transcripts will be examined to identify key themes and subthemes. To ensure validity, a proportion of transcripts (approximately 20%) will be double-coded by a second qualitative researcher, and any discrepancies resolved by discussion. Thematic analysis will be supported by NVivo software.

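### Recovery and recurrence times after episodes that begin in follow-up are conditional on the primary-outcome event, so the promised arm effects on them are open to selection bias

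*Protocol article*

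**What the plan says.** Box 3 (Secondary outcomes) lists four measures derived from the LIFE interview: number of depression-free weeks, duration of depression-free periods, and "time to recovery from depressive episodes and time to recurrence of depressive episodes in the 9-month follow-up period". The Secondary outcomes section gives the purpose of these outcomes: "These assess the potential effect of the intervention on depression severity and recovery". The Analyses section ends its paragraph on secondary outcomes with "Main group effects and 95% CIs will be presented for all outcomes" and makes no exception.

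The primary outcome comes from the same weekly LIFE ratings: "A DSR score of >4 for at least 2 weeks will define a depressive episode" (Depressive episodes). The Sample size section expects the proportion with an episode to differ between arms: "expected event rate probabilities at follow-up of 0.327 (control) and 0.211 (intervention".

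The article does not state an analysis population or time origin for recovery or recurrence, and does not say that either is conditional on an episode.

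**The concern.** A YP whose first follow-up episode begins after randomisation has a recovery time only because that episode happened. Recurrence after that episode requires the episode and then a recovery. Having the episode is the primary outcome, which the intervention is meant to change. If it does so, the YP with episodes in the two arms have passed through different filters, and comparing their recovery is no longer a randomised comparison.

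If prevention removes relatively more episodes in YP who would have recovered quickly, the remaining intervention-arm cases are slower to recover on average. An intervention with no effect on recovery could then appear to slow it. A 95% CI would not reveal this, because it covers sampling error and not selection.

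**Working it through.** **1. Check that the article's event rates can be used.** Inputs from Sample size and Trial design: up to 400 randomised 1:1, "with an assumed 10% attrition rate at 9 months", event probabilities 0.327 and 0.211, one-sided alpha 0.05.

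- Analysable per arm: 200 × 0.9 = 180.
- Expected events: 180 × (0.327 + 0.211) = 96.8.
- Schoenfeld power at HR 0.60: Φ(√96.8 × |ln 0.60| / 2 − 1.645) = Φ(0.87) = 80.7%.
- Freedman power: Φ(√96.8 × 0.40 / 1.60 − 1.645) = Φ(0.82) = 79.3%.
- Article: "we estimate statistical power as 79.9% to detect a difference of at least HR=0.60 between study arms".
- At HR 0.56 the intervention risk under proportional hazards is 1 − 0.673^0.56 = 0.199, giving 94.7 events. Power is 88.0% (Schoenfeld) and 86.4% (Freedman). Article: "A HR of 0.56 (equivalent to a 12% difference between study arms) will attain 87.0% power".

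The stated power is reproduced to within about one percentage point, so the rates are a sound basis for counting cases.

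**2. Count who has a recovery time from a new episode.**

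- Control: 180 × 0.327 = 59.
- Intervention: 180 × 0.211 = 38.
- Together 97 of 360, or 27%. The other 73% have no new-episode recovery time, and recurrence after such a recovery is rarer still.

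**3. Gauge the possible bias when the intervention does not affect recovery.** Simulation, 2 million per arm. A latent vulnerability (standard normal) raises the log-hazard of onset with slope b and lowers the log-hazard of recovery with slope c. Onset risks over 39 weeks (9 months) are calibrated to 0.327 and 0.211. Mean recovery time at average vulnerability is 12 weeks. The arm has no effect on recovery, so the true ratio is 1.00. The estimate is recoveries divided by time at risk of recovery, intervention over control, with follow-up censored at week 39. The values of b, c, the 12 weeks and the interaction are assumptions.

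| Scenario | Apparent recovery rate ratio |
|---|---|
| Vulnerability does not affect recovery (c = 0; b = 0.5, 1.0, 1.5) | 0.996, 1.002, 1.000 |
| Shared cause, b = 0.5 (c = 0.5, 1.0) | 0.985, 0.980 |
| Shared cause, b = 1.0 (c = 0.5, 1.0) | 0.966, 0.934 |
| Shared cause, b = 1.5 (c = 0.5, 1.0) | 0.930, 0.890 |
| Shared cause and weaker prevention in more vulnerable YP, b = c = 0.5 (interaction 0.3, 0.6) | 0.886, 0.804 |
| Same, b = c = 1.0 (interaction 0.3, 0.6) | 0.808, 0.723 |

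**4. Compare with sampling error.** In the last run 55% of control and 46% of intervention cases recover: 59 × 0.55 ≈ 32 and 38 × 0.46 ≈ 17. The SE of the log ratio is about √(1/32 + 1/17) = 0.30. The shift ln 0.723 = −0.32 is about 1.1 SE. At a ratio of 0.89 the shift of −0.12 is about 0.4 SE.

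**5. Check whether later onset matters separately.** With constant hazards over 39 weeks, mean onset among cases is 1/λ − 39(1 − p)/p, where λ = −ln(1 − p)/39. This gives 18.2 weeks for p = 0.327 and 18.7 weeks for p = 0.211, a difference of about half a week.

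**The case against.** **Not every recovery or recurrence time is conditional on a new episode.** A reader might infer that these times exist only in YP who develop an episode after randomisation. The eligibility criteria do not establish that. They exclude a current diagnosis by a health professional and current specialist treatment, not an undiagnosed episode. A raised CES-D score is one entry route, and the baseline diagnostic interview is not stated as an exclusion. A YP already in an episode at randomisation has a recovery time starting at baseline. A past episode is another entry route, so a first follow-up episode in such a YP can be read as a recurrence in a baseline-defined group. This stands and limits the point. But the article restricts neither outcome to these groups, so new episodes remain in the comparison.

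**Bias is not certain.** A reader might also infer that the estimates must be biased, and more so the better the intervention works. With no shared cause of onset and recovery the bias is about nil, and the larger shifts need prevention to be weaker in vulnerable YP. This stands. Both conditions are plausible on the article's own account, however. The Mediators section allows that some mediators may act on both the onset and the maintenance of depression. The Introduction reports a weaker effect in the earlier trial when the index parent was currently depressed.

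**Later onset is not a separate source of bias of any size.** The difference is about half a week. If YP not yet recovered at month 9 are censored, shorter observation mainly costs precision.

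**The analysis plan may settle it.** The article is condensed, the analysis plan is not shown, and the sentence on all outcomes closes a paragraph about repeated-measures, linear mixed and logistic models. The analysis set for these outcomes could be defined there. Still, the article names recovery as something the intervention is assessed on and promises an effect for every outcome. That is a stated commitment, not an omitted detail.

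**Conclusion.** The concern holds for episodes that begin after randomisation. There, arm effects on time to recovery and time to recurrence would compare about 59 with 38 YP selected by the primary outcome, and they are open to bias. With no true effect on recovery, the apparent rate ratio ran from about 1.00 down to 0.72, depending on assumed links between onset, recovery and response to prevention. In every shared-cause scenario run, the error pointed towards apparent slowing of recovery. It was at most about one standard error, so the issue is a systematic error that the interval does not reflect, not a likely false significant result.

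The documents do not support saying that these estimates are biased outright, or that the problem covers YP in an episode at randomisation or baseline-defined groups with a past episode. The primary outcome and the sample size are unaffected.

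**What to change.** Exempt time to recovery and time to recurrence after new episodes from the statement about effects for all outcomes. Report them descriptively by arm, with the number of YP contributing, labelled as conditional on having had an episode. If a comparison of recovery among YP in an episode at randomisation, or of recurrence among YP with a past episode, is wanted, define those groups from baseline data.

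Rest the randomised comparison of depression course on number of depression-free weeks, already in Box 3, in all YP with LIFE data. The weekly probability of being in an episode is an alternative. Both come from the weekly LIFE ratings already planned.

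The cost is wording in the analysis plan, with no new data. The downside is that no effect estimate would be given for recovery or recurrence after new episodes.

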
### Mediators

The logic model (figure 2) shows hypothesised mediators of change for the intervention. These include measures of cognitive change, behavioural activation, perceived coping efficacy, perceived stress and quality of the parent-child relationship indexed by warmth, conflict and openness. Mediators are either targeted by the intervention; evidence indicates they may contribute to the onset and maintenance of depression and/or index environmentally mediated intergenerational links between parent and YP depression.^1645^,^47^ Possible mediators will be measured at baseline, 3 months and 9 months post randomisation. Qualitative interviews will be conducted to explore participant perceptions of possible mechanisms of action and non-specific mediators such as perceptions of the possibility of change and the group/therapeutic alliance.^45^

**Figure 2 F2:**
[figure not shown]
Logic model of SWELL intervention on depression, mental health and functioning in the young person. ARI, Affective Reactivity Index; BADS-SF, Behavioural Activation Scale for Depression - short form; CBQ, Conflict Behaviour Questionnaire; CBT, Cognitive Behavioural T﻿Cognitive Behavioural Therapy; CES-D, Centre for Epidemiological Studies-depression scale; cGAS, Children’s Global Assessment Scale; CRPBI, Child’s Report of Parent Behaviour Inventory; DAS-C, Dysfunctional Attitudes Scale for Children; EQ-5D-Y, EuroQol Quality of Life 5 Dimensions; GSE, Generalised Self-Efficacy Scale; LIFE, Longitudinal Interval Follow-Up Evaluation; NICE, National Institute for Health and Care Excellence; PHQ-9, Patient Health Questionnaire-9; PSS, Perceived Stress Scale; RCADS, Revised Children’s Anxiety and Depression Scale; SWELL, Skills for adolescent WELLbeing.

### Additional measures

Table 2 includes baseline measures of demographic factors, depression symptom severity and comorbidity, stressful life events and service use in the YP (to allow a future economic evaluation) at baseline and follow-up. Questionnaires and interviews completed by the parent will provide information on baseline parental depression and the course of the parent’s depression throughout the study, plus parental anxiety and functional impairment.

### Data linkage

Consent will be sought from participants for anonymised data linkage to routine health and education records. This will allow longer-term follow-up in the future where treatment in health records would be the primary outcome.

Feasibility and acceptability	At 3-month follow-up, all young people in the intervention group and their parents will complete online questionnaires about their experience of receiving the intervention.Semistructured qualitative focus groups will be conducted with a subgroup of young people (n=16) and parents (n=8). Topic guides will ask about their experiences of receiving the intervention, with a focus on acceptability of online delivery and their views on potential implementation and scalability.There will also be qualitative interviews/focus groups with trial therapists (n=4) about their experiences of delivering the intervention and their perspectives on factors affecting future implementation.	At baseline, all parents who have received treatment optimisation will complete online questionnaires about their experience of receiving the intervention.Semistructured qualitative interviews/focus groups will be conducted with parents who received treatment optimisation (n=8) to explore the acceptability of this intervention.
Intervention mechanisms	The semistructured qualitative interviews/focus groups mentioned above will also help to examine underlying intervention mechanisms for the young person, including the CBT intervention for the young person and any perceived effect on family functioning or on the young person of PTO. We will seek the views of participating young people, parents and trial therapists and psychiatrists about what the active ingredients of the intervention might be. We will include prompts to assess active ingredients not captured in quantitative measures, including addressing stigma and non-specific mediators (eg, qualities of the group or the therapeutic alliance). We will also assess participant views of what helped and any potential barriers or implementation considerations.	
Experiences of and feedback on trial processes	Focus groups will be conducted with young people and parents about their experiences of trial processes. This will include the intervention groups described above and focus groups of young people (n=8) and parents (n=8) allocated to the control arm.	

In addition to exploring the SWELL intervention and PTO fidelity, adherence, feasibility and acceptability and intervention mechanisms, semistructured qualitative interviews/focus groups will be conducted with young people and parents randomised to the usual care arm regarding their experience of trial processes as part of the nested process evaluation.

